**Method:**

A prospective cohort study involving 132 consecutive participants. Preoperatively, participants undergoing arthroscopic subacromial decompression and/or excision of the distal clavicle and/or rotator cuff repair will complete questionnaires about their levels of shoulder pain using a numerical rating scale from 0 to 10, and answer a Patient Health Questionnaire – 9 depression questionnaire. Postoperatively, the participants’ pain levels will be self-assessed at two, five and seven days and weeks four, seven and ten. They will complete the depression questionnaire twice, at the time of their routine first and final postoperative appointments with the treating surgeon. At the final appointment, approximately three months postoperatively, the treating surgeon will clinically diagnose participants as having a postoperative stiff shoulder or not. Their shoulders’ range of motion will be measured. The incidence of postoperative stiff shoulder will be determined, both pain and depression will be analysed as predictors for its development and incidences determined by different objective criteria will be compared.

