#### Outcome assessment

Baseline data collected from participant will include sex, age, dominant arm, shoulder side undergoing operation, history of diabetes mellitus and present treatment for diabetes mellitus, third party compensation status, history of depression, time since diagnosis of depression, whether participant is presently receiving treatment for depression and whether and type of previous surgery the participant has had on the shoulder undergoing operation (see Additional file 1).

Preoperatively participants will have range of motion assessed and be asked to complete a questionnaire encompassing pain, analgesia, sleep and mood (see Additional file 2). Range of motion of the shoulder will be assessed for each of the following planes of motion: active elevation, passive glenohumeral abduction with stabilisation of the scapula, passive external rotation in adduction and passive internal rotation in 90°, or maximal, abduction. This will be done using a goniometer. Average pain, worst pain at rest whilst seated with the arm at the side, worst pain with movement and worst pain at night over the last 24 h will be assessed using a visual numerical rating scale (NRS). The NRS pain scale is an 11 point scale where 0 = no pain and 10 = worst possible pain. Participants will be asked to detail the types of analgesia, dosage and treatment they have received in the last 24 h. Sleep will be assessed using a visual NRS sleep scale where 0 = worst possible sleep and 10 = best possible sleep. Participants will be asked what type and dosage of mediation (if any) they have taken to help them sleep in the last 24 h. Last, participants will be provided with a Patient Health Questionnaire – 9 (PHQ-9) that will assess their mood and depressive symptoms over the past two weeks and they will be classified as depressed or not depressed according to the DSM-IV criteria for a major depressive episode [35]. The PHQ-9 has a sensitivity of 98 % and specificity of 80 % for major depressive disorder when using the cutoff of 11 points or greater and allows for stratification of depression severity [35, 36].

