Postoperatively participants will be clinically followed up at multiple time points. The operating surgeon will assess them at both their first and final postoperative consultations. The first consultation around the time of suture removal, and the second consultation three months after the operation. In addition the investigator will contact them by phone postoperatively on days two, five and seven and additionally at weeks four, seven and ten. At both postoperative surgeon clinical assessments the participants will asked to complete the PHQ-9. This will assess their mood over the previous two weeks. At their final postoperative consultation the range of motion of their treated shoulder will also be assessed. The senior surgeon will determine clinically whether or not the patient has ‘postoperative stiff shoulder’.

During each of the follow up phone calls, participants will be asked to complete the same pain questionnaires as preoperatively with the use of a verbal NRS and to detail the types of analgesia, dosage and any other treatment they have received in the last 24 h. The preoperative sleep assessment, using a verbal NRS, will be preformed postoperatively at these times. Participants will be asked what type and dosage of mediation (if any) they have taken to help them sleep in the last 24 h. Lastly patients will be asked to describe their mood over the past 24 h and also describe any events or stressors that may have impacted upon their pain, sleep or mood. This will be recorded on specifically designed form (see Additional file 3). Therefore each participant will have six phone assessments over the three months.

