### Analysis

The incidence of postoperative stiff shoulder will be determined using the treating surgeon’s clinical diagnosis informed by the Buchbinder criteria of restriction of motion of greater 30° in two or more planes of shoulder motion [40].

Patient demographics, baseline range of motion, pain, sleep and depression scores and outcome data will be presented for both outcome groups (postoperative stiff shoulder and no postoperative stiff shoulder).

The principal analysis will involve assessing whether or not a relationship exists between average pain scores and development of postoperative stiff shoulder. This will be by determining if there is a significant difference of the mean of the “average pain scores over the last 24 h” between both outcome groups at each recorded time point and over predetermined periods (first week postoperatively, first month postoperatively and from week four to ten postoperatively), adjusted for multiple comparisons using the Holm’s step down procedure [41].

Secondary analysis will assess depression and its relationship with PSS. A history of depression diagnosis as well as active depression at each time point, as assessed by the PHQ-9, will be assessed for an association with a diagnosis of PSS adjusted and not adjusted for baseline depression, and adjusted for multiple comparisons using the Holm’s step down procedure [41].

This study will also report the incidences of postoperative stiff shoulder after rotator cuff repair as well as subacromial decompression and excision of the distal clavicle not in association with rotator cuff repair.

Finally a series of range of motion criteria will be used to objectively determine a range of incidences of PSS in the same cohort (Table 1).

**Table 1 Tab1:** Criteria for diagnosing postoperative stiff shoulder

Criteria for diagnosing postoperative stiff shoulder
Clinician’s diagnosis
Range of motion thresholds in two planes, both required • Active elevation <100 degrees AND • Passive external rotation <30 degrees
Range of motion thresholds in two planes, at least one required • Active elevation <100 degrees OR • Passive external rotation <30 degrees
Restricted range of motion compared to contralateral side, at least two planes • Restriction of >30 degrees in TWO or more planes of movement
Restricted range of motion compared to contralateral side, at least three planes • Restriction of >30 degrees in THREE or more planes of movement

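### The only postoperative PHQ-9 before the stiff-shoulder diagnosis has a two-week recall that may reach back before surgery; the only later one is taken at the diagnostic visit

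*Protocol article*

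**What the plan says.** Outcome assessment in the protocol article has a preoperative PHQ-9, "that will assess their mood and depressive symptoms over the past two weeks", and two postoperative ones: "At both postoperative surgeon clinical assessments the participants will asked to complete the PHQ-9". The two visits are timed as "The first consultation around the time of suture removal, and the second consultation three months after the operation". The recall of the postoperative questionnaire is explicit: "This will assess their mood over the previous two weeks".

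The outcome is fixed at the second of these visits. The Abstract (Method) says: "At the final appointment, approximately three months postoperatively, the treating surgeon will clinically diagnose participants as having a postoperative stiff shoulder or not".

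Between the visits there are telephone contacts: "the investigator will contact them by phone postoperatively on days two, five and seven and additionally at weeks four, seven and ten". The mood item described for them is not the PHQ-9: "Lastly patients will be asked to describe their mood over the past 24 h".

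The Analysis section then plans that "active depression at each time point, as assessed by the PHQ-9, will be assessed for an association with a diagnosis of PSS", with and without adjustment for baseline depression and with Holm's correction. History of depression is tested as well. The Discussion lists the ability to study a temporal relationship between depression and PSS among the strengths of the study.

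**The concern.** A temporal claim about postoperative depression needs a measure that lies after surgery and before the diagnosis. Of the three PHQ-9 occasions, one is preoperative and one is at the diagnostic visit. Only the suture-removal PHQ-9 is left, and its position relative to the operation is loose. It is tied to a clinical event, while its recall is a fixed 14 days. If the visit comes before day 14, the score mixes mood before and after the operation, in a proportion that can differ between patients. If it comes on or shortly after day 14, the score describes the first weeks of recovery, when pain and sleep are disturbed by the operation. Early pain is also the exposure in the study's first hypothesis, so the two are hard to tell apart.

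The Analysis section treats active depression at every PHQ-9 time point alike. It does not separate a measure that may straddle surgery, or one taken together with the outcome, from a predictor. At stake is how far the study can say that depressed mood after surgery comes before PSS and does not merely accompany it. Later analysis cannot supply a measurement that was never taken.

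**Working it through.** The plan states no figure on this point, so there is none to reproduce. The check sets the schedule out in time and calculates the recall windows.

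**Inputs from the document.** PHQ-9 recall: 14 days (Outcome assessment). PHQ-9 occasions: preoperative, first consultation, final consultation (Outcome assessment). Diagnosis: final consultation at about three months (Abstract, Method). Calls: days 2, 5 and 7 and weeks 4, 7 and 10 (Outcome assessment).

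**Assumptions.** The postoperative day *d* of the first consultation is not stated; the range used is day 7 to day 14. Three months is taken as 13 weeks, or day 91.

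**Step 1: order of the measures**

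| PHQ-9 | Position relative to surgery | Position relative to diagnosis |
|---|---|---|
| Preoperative | before | before |
| First consultation | after, but the window may reach back before surgery | before |
| Final consultation | after | same visit |

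PHQ-9 assessments after the first consultation and before the diagnostic visit: 0.

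**Step 2: preoperative share of the first postoperative window**

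Preoperative days = max(0, 14 − *d*); share = preoperative days / 14.

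| Visit day *d* | Preoperative days | Share |
|---|---|---|
| 7 | 7 | 7/14 = 50% |
| 10 | 4 | 4/14 = 29% |
| 12 | 2 | 2/14 = 14% |
| 14 or later | 0 | 0% |

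The window straddles surgery only if *d* < 14.

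**Step 3: overlap with the baseline window.** If the baseline PHQ-9 is completed *b* days before surgery, its window ends *b* days before surgery, and the first postoperative window starts 14 − *d* days before it. The two overlap only if *b* < 14 − *d*. For a visit on day 10 the baseline must be less than 4 days before surgery; for day 12, less than 2 days. The article gives no *b*, so overlap is possible but not shown.

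**Step 4: the three-month PHQ-9.** Its window is about day 91 − 14 = 77 to day 91 and ends at the visit where PSS is diagnosed. An association found there cannot show which came first.

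**Step 5: a PHQ-9 at the week-4 call.** Window: day 28 − 14 = 14 to day 28. No preoperative days are included. Interval to the diagnostic visit: 91 − 28 = 63 days, about two months.

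**The case against.** The strongest reply is that the depression hypothesis does not need a postoperative measure. As worded in the Background, it says only that patients with depressed mood are more likely to develop PSS. The pain hypothesis, by contrast, is limited to the first postoperative month. The stated aim concerns the perioperative period, and a window that spans surgery is compatible with that. The preoperative PHQ-9 and the history of depression both come before the outcome, and the analysis adjusted for baseline depression deals in part with carry-over from preoperative days. All of this stands, and it limits the point to the postoperative part of a secondary analysis.

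A second reply is that the visit day may be fixed in the full protocol, which the article condenses. That also stands: the absent day is not itself a fault. A visit on day 14 or later would remove the straddle and leave a wholly postoperative score about 11 weeks before diagnosis (91 − 14 = 77 days). It would not change the fact that this is the only postoperative PHQ-9 before diagnosis, or that at day 14 it covers the first two weeks of recovery.

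Third, the mood answers at the calls go on a dedicated form (Additional file 3), which is not shown. One cannot say that they are unusable, only that the article describes no PHQ-9 there and that the planned analysis defines active depression by the PHQ-9.

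Last, week 4 is still within the month targeted by the pain hypothesis, so a PHQ-9 then would not be free of confounding by pain and sleep. This is true. What it does secure is a window wholly after surgery and clear of the first two weeks.

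**Conclusion.** The point holds in a limited form. The only postoperative PHQ-9 before the diagnosis may include preoperative days (50% of the window at day 7, 29% at day 10, none from day 14, with the day itself assumed) and otherwise covers early recovery. The only later PHQ-9 is concurrent with the diagnosis and gives no support to the temporal claim in the Discussion. That the last PHQ-9 and the diagnosis share a visit, and that none is scheduled between the two consultations, does not depend on the assumed day.

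A reader might infer three stronger things that the document does not support:

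- That no clean postoperative depression measure precedes the diagnosis. On window overlap this is true only of visits before day 14.
- That the depression hypothesis cannot be tested prospectively. It can, through the preoperative PHQ-9 and the history of depression.
- That baseline adjustment is futile because the two windows overlap. Overlap also requires a baseline PHQ-9 completed fewer than 14 − *d* days before surgery, which is not stated. Adjustment helps in part.

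The principal pain analysis and the incidence estimates are unaffected. This is an inexpensive improvement to a secondary aim.

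**What to change.** 1. Add the PHQ-9 to the existing week-4 telephone call and include that score as a postoperative depression predictor of PSS.
2. Keep the suture-removal PHQ-9 in the analysis and record the postoperative day of completion, so that the preoperative share of each window is known. There is no shown need to demote it to a descriptive measure.
3. Report the three-month PHQ-9 as a cross-sectional association with PSS, not as a predictor, and word the temporal claim in the Discussion to match.

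**Cost.** Nine extra questions in one scheduled call, with no new visit. It is feasible for all participants, because inability to answer by telephone is already an exclusion criterion. The downsides are telephone administration at that one time point and one more test in the Holm family (two if the analyses with and without baseline adjustment are both counted). As an illustration, assume one test per predictor: history plus three PHQ-9 occasions makes four tests and a first Holm threshold of 0.05/4 = 0.0125; a fifth test lowers it to 0.05/5 = 0.010.

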## Background

The enigmatic “frozen shoulder”, since its description by Duplay in 1872, has lacked a consensus definition until 2011 when Zuckerman established a consensus definition and classification system of frozen shoulder where he classified cases as either primary (idiopathic) or secondary [1–3]. He further delineated secondary frozen shoulder according to its associated aetiology, in which postoperative stiff shoulder (PSS), if viewed as a type of “frozen shoulder”, would fall under the intrinsic category. A survey of the members of the American Shoulder and Elbow Surgeons found that both this definition and classification were well received [3].

Zuckerman’s accepted definition of frozen shoulder is “a condition characterized by functional restriction of both active and passive shoulder motion for which radiographs of the glenohumeral joint are essentially unremarkable except for the possible presence of osteopenia or calcific tendonitis.” This descriptive definition is also an appropriate definition for postoperative stiff shoulder in the setting of patients who have recently undergone shoulder surgery.

Although the clinical features of frozen shoulder and PSS have been well characterised, a consensus of objective clinical diagnostic criteria has not been established [4]. A multitude of criteria has been published demonstrating a variety of methods used to diagnose patients with this condition. These include a marked variety of range of motion measurements with different thresholds [5–19] and clinical judgement with and without guiding criteria [11, 20–25] and contentiously patient satisfaction with outcomes [26]. The lack of universal, or even widely used, definitive criteria makes accurately comparing and synthesizing results from studies assessing frozen shoulder and/or PSS difficult to impossible and is possibly a reason behind reported rates of PSS varying between 4.9 and 23 % [5, 10, 13, 26]. Additionally in patients with suspected PSS it may be difficult to clinically distinguish pathological stiffness due to capsulitis from restricted motion due to a tight tendon repair and different criteria may over or under diagnose true pathology.

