### Setting and participants

Over a six-month period participants will be recruited from the private community practice of a single orthopaedic shoulder surgeon ([name]) in Melbourne, Australia. Recruiting patients from a single shoulder surgeon eliminates the potential confounding factors of surgical skill, technique, experience and postoperative care. All surgery will be performed by this surgeon.

All eligible patients who fulfil the selection criteria during the recruiting period will be invited to participate. Inclusion criteria will be all patients aged 18 to 90 who will be undergoing rotator cuff repair, subacromial decompression or excision of the distal clavicle by the surgeon. Exclusion criteria will be: (i) grade IV gleno-humeral arthritis of the shoulder undergoing operation diagnosed on arthroscopy (ii) preoperative shoulder stiffness (iii) concomitant surgical procedure except for rotator cuff repair, subacromial decompression, distal clavicular resection, debridement, bursectomy, synovectomy or biceps tenodesis (iv) superior labral tear from anterior to posterior (SLAP) repair (v) inability to answer questions by phone (vi) poor English language skills.

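### The stiff-shoulder outcome is the operating surgeon's judgement, made at the visit where the PHQ-9 is completed, and nothing stated keeps the predictors from influencing borderline diagnoses

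*Protocol article*

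**What the plan says.** All points are from the protocol article.

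- **One surgeon throughout.** Setting and participants: "All surgery will be performed by this surgeon". Outcome assessment: "The operating surgeon will assess them at both their first and final postoperative consultations".
- **The diagnosis.** Outcome assessment: "The senior surgeon will determine clinically whether or not the patient has" a postoperative stiff shoulder. The Abstract agrees that, at the final appointment, "the treating surgeon will clinically diagnose participants as having a postoperative stiff shoulder or not". The Analysis section describes a "clinical diagnosis informed by the Buchbinder criteria of restriction of motion of greater 30° in two or more planes of shoulder motion".
- **Depression.** "At both postoperative surgeon clinical assessments the participants will asked to complete the PHQ-9". The second of these assessments is the diagnostic visit.
- **Pain.** Postoperative scores are collected by phone by the investigator, who is named separately from the operating surgeon. The last call is at week ten.
- **Analyses.** The principal analysis compares mean pain between the PSS and no-PSS groups. The secondary analysis tests depression for association with a diagnosis of PSS.
- **Range-of-motion criteria.** "Finally a series of range of motion criteria will be used to objectively determine a range of incidences of PSS". The Background adds that their sensitivity and specificity will be assessed against the surgeon's diagnosis. They are not used as the outcome in the pain or depression analyses.

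**The concern.** The study asks whether pain and depression predict PSS. The label that defines PSS is assigned by a clinician who has followed the patient since surgery, at a visit where one of the predictors is recorded. Misclassification unrelated to the predictors mostly dilutes an association. Misclassification that depends on them can create one. If high pain or low mood tips a borderline shoulder towards a PSS label, part of any association found is built into the outcome.

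Borderline cases are to be expected. The Background says that "it may be difficult to clinically distinguish pathological stiffness due to capsulitis from restricted motion due to a tight tendon repair". The planned PSS group is small, so a few such decisions would move the group means. The Discussion hopes to use pain as a marker for early intervention, and that use depends on the outcome label being free of the predictor.

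**Working it through.** **1. What is fixed and what is left open**

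| Question | What the article states |
|---|---|
| Who diagnoses PSS? | The operating surgeon, clinically |
| Does a rule decide? | No; more than 30° in two or more planes informs the judgement |
| Is the PHQ-9 completed at the same visit? | Yes |
| Does the surgeon see the PHQ-9 or the phone scores before diagnosing? | Not stated either way |
| Is there a masked or second assessor? | None stated |
| Are pain or depression tested against a Table 1 motion criterion? | No; these give incidences and accuracy only |

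**2. The planned group sizes**

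Inputs from Sample size: difference 2, SD 2.20, power 0.80, α 0.05 (taken as two-sided), PSS incidence 10% (ratio 9:1).

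PSS n = (1 + 1/9) × (1.960 + 0.842)² × 2.20² / 2² = 1.111 × 7.85 × 1.21 ≈ 10.6, so 11. Non-PSS = 99, total 110, as stated. Exact t-test power at 11 + 99 is 0.809. The stated 132 is 110 × 1.2. The point here does not depend on the sample size; these figures only set the scale.

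**3. Illustration by relabelling (assumed values)**

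No true association; 11 PSS and 99 non-PSS, both with mean pain 0 relative to the average. Three non-PSS patients, each 3 points above average, are labelled PSS.

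- PSS mean = (11 × 0 + 3 × 3)/14 = 9/14 = 0.643
- Non-PSS mean = −9/96 = −0.094
- Difference = 0.643 + 0.094 = 0.74 points; 0.74/2 = 37% of the target difference
- SE = 2.2 × √(1/14 + 1/96) = 0.63
- t = 0.74/0.63 ≈ 1.17, p ≈ 0.24

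The analysis also applies Holm's procedure. Six calls plus three periods give at least nine tests, so the smallest p-value would have to fall below about 0.05/9 = 0.0056.

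**4. Illustration by simulation (assumed values)**

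N = 110, true stiffness 10%, pain SD 2.2 and independent of stiffness, high pain meaning above the mean, one unadjusted t-test at 0.05, 10,000 runs.

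| Diagnosis | Spurious difference | Rejection rate |
|---|---|---|
| No error | about 0 | 5.0% |
| 5% false positives whatever the pain; sensitivity 90% | about 0 | 4.8% |
| False positives 2% (low pain) v 5% (high pain); sensitivity 90% | 0.23 | 6.5% |
| False positives 2% v 8%; sensitivity 90% | 0.42 | 10% |
| False positives 2% v 10%; sensitivity 80% v 95% | 0.63 | 18% |

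Error that ignores pain does no harm to the type I error, while error that follows pain does. The error rates are assumptions; the article gives none. Holm's adjustment addresses multiplicity, not this bias.

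**The case against.** The case on the other side is substantial, and most of it stands.

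- **The diagnosis is not free-floating.** It is anchored to a numeric motion criterion. Discretion remains only around that anchor.
- **Knowledge of the predictors is not documented.** A reader might infer that the surgeon diagnoses with the pain record and PHQ-9 in hand. The article does not say so: the investigator makes the calls, and nobody is said to show the surgeon the self-completed PHQ-9. A fuller protocol might describe how forms are handled.
- **The route is weakest for the principal hypothesis.** That hypothesis concerns pain in the first month. At three months the surgeon would mainly hear about current pain, although the visit around suture removal gives some exposure to early pain. Among the depression measures, only the final-visit PHQ-9 is completed at the diagnostic visit.
- **The clinical diagnosis is a deliberate reference.** The Background explains that no consensus objective criterion exists. Its remark about capsulitis and tight repairs applies to motion thresholds too, so it does not show that they are better than judgement.

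What remains is that the article states how the outcome is assigned and what the motion criteria are used for. On those statements, no safeguard separates predictor from outcome and no analysis would reveal whether the separation failed.

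**Conclusion.** The point holds as a risk of bias that is possible and unprevented. It is most direct for the final-visit PHQ-9, and possible but undocumented for pain. Bias is not shown.

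A reader might go further and infer that a few borderline decisions would dominate the result or manufacture a positive finding. The figures do not support that. The three-patient example shifts the difference by 0.74 points, a little over one standard error, and would not reach significance even without Holm's adjustment. The simulated rejection rates of 6.5% to 18% rest on assumed, pain-dependent error rates and a single unadjusted test. They show direction and plausible scale, not what will happen in this study.

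The sample size is unaffected, and using the surgeon's diagnosis as the main outcome is a defensible choice. The change below is an inexpensive safeguard, not the correction of an error.

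**What to change.** 1. **Order of steps at the final visit.** Record range of motion and the PSS diagnosis before the surgeon sees that visit's PHQ-9. Keep the phone pain and mood forms with the investigator until the diagnosis is recorded.
2. **Sensitivity analysis.** Repeat the pain and depression analyses with a Table 1 threshold criterion as the outcome (active elevation below 100° and/or passive external rotation below 30°), and report it beside the surgeon-diagnosis result. Use the contralateral-comparison criteria only if the other shoulder is also measured, because Outcome assessment states final motion only for the treated one.

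**Cost.** A change of sequence at one visit and one repeated set of analyses on measurements already planned, with no extra assessor.

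**Limits.** The surgeon may still hear about pain in conversation. Both threshold criteria include active elevation, which pain can itself restrict, and the article does not say who measures final motion. The repeat is therefore a robustness check, not a pain-free reference. Agreement would strengthen the main result; disagreement would tell readers that it depends on how PSS is defined.
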